### Analysis plan

Data will be downloaded from the CDC website (https://www.cdc.gov/nchs/data_access/vitalstatsonline.htm) for the most recent year with available data (2023 at the time of writing this protocol).

If data missingness for one or more explanatory or outcome variables occurs in > 5 % and < 40 % eligible births then multiple imputation will be considered. Potential mechanisms of missingness and the relationship of missingness to the outcome and covariates will be assessed when deciding to conduct multiple imputation or a complete case analysis.

If multiple imputation is required, we will use fully conditional specification with five imputed datasets. Any multiple imputation will include all explanatory and outcome variables, and any interaction terms. Interdependencies amongst variables will be handled with the passive imputation method. P-values for the likelihood ratio test for each variable in each imputed dataset will be pooled using the median p-value rule.

Using Robust Poisson Regression, maternal pre-pregnancy BMI will be modelled on the primary outcome of cesarean delivery and other covariates (listed below) excluding BMI gain during pregnancy. Maternal BMI at the time of delivery will be modelled on the same covariates. Of these two models, the model with the lowest Akaike Information Criterion (AIC) will be used to select the BMI variable with the greatest explanatory power to be used in subsequent analyses (either pre-pregnancy or delivery BMI). This variable is referred to as ‘Maternal BMI’ in all subsequent analyses below. The two models will also be compared using the log-likelihood test.

Pre-pregnancy BMI will be categorized according to the United States Centers for Disease Control and Prevention which classifies adult BMI as underweight (BMI < 18.5), normal weight (BMI 18.5 – 24.9), overweight (BMI 25-19.9), Class 1 obesity (BMI 30-34.9), Class 2 Obesity (BMI 35-39.9), and Class 3 Obesity (BMI 40 or more) [20]. Delivery BMI will be classified such that the same numbers of women will be in each class (i.e., the same quantile cut-offs will be used for pre-pregnancy and delivery BMI groups). This is expected to account for weight gain in pregnancy including factors such as fetal weight and amniotic fluid volume. Based on the exploratory analysis for 2022 data, BMI gain and gestational weight gain will be treated as linear splines with one knot placed at 5 kgm^-2^ and at 12 kg respectively.

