As nulliparous women are an important group who contribute to the first/primary cesarean delivery rate, we will test for interaction (effect modification) between maternal BMI gain and parity, and maternal BMI and parity. If interaction is present (BMI or BMI gain have a different association with cesarean delivery depending on parity), then the primary analysis will be restricted to nulliparous women only and we will conduct secondary analyses for parous women.

For the primary outcome of cesarean delivery, backward stepwise Robust Poisson Regression will be used. The following variables will be included in the multivariable Poisson regression model as potential predictors of cesarean section:•Maternal BMI (not eligible for exclusion in the backwards stepwise regression).•Gestational BMI gain (not eligible for exclusion in the backwards stepwise regression)•Parity•Maternal age (continuous)•Gestational age•Maternal height•Maternal race•Cigarette smoking•Payment type•Trimester of onset of maternity care (4 categories: first, second or third trimester, or no•antenatal care)•Education (categorized)•Fertility treatment used•Diabetes (3 categories: pre-pregnancy, gestational, none)•Hypertension in pregnancy (dichotomous)•Interaction terms: BMI x parity and BMI gain x parity

Birthweight will not be included as an explanatory variable because it was considered that fetal weight may be on the causal pathway between BMI or BMI gain and cesarean delivery. Therefore, the relative risks for BMI or BMI gain for the primary outcome of cesarean delivery will include any indirect effect mediated through fetal weight.

If Robust Poisson Regression Models do not converge then alternative regression methods will be considered.

For secondary outcomes, all explanatory variables will be retained in the model. Stepwise backward regression will not be used. No interaction terms will be used.

For the secondary outcome of third or fourth degree perineal laceration, the data will be limited to vaginal births only and the following covariates will be used: BMI at delivery, BMI gain, parity, maternal age, gestational age, maternal height, maternal race, mode of delivery (unassisted/vacuum/forceps).

For the secondary outcome of trial of labour, the following covariates will be used: BMI at delivery, BMI gain, parity, maternal age, gestational age, maternal height, maternal race, payment type, education, trimester of onset of maternity care, use of ARTs, and gestational diabetes.

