For the secondary outcome of preterm birth, the same covariates will be used as for the primary outcome except gestational age will be removed and previous preterm birth will be added.

For the secondary outcome of NICU admission, the same covariates will be used as for the primary outcome of cesarean delivery.

For the uncommon or rare secondary outcomes of unplanned hysterectomy, maternal admission to the ICU, 5 min Apgar Score < 4, assisted ventilation immediately following delivery and for more than six hours, antibiotics for suspected neonatal sepsis, and neonatal seizure or serious neurological dysfunction, the same covariates will be used as for the primary outcome, if there are at least five events per variable. If there are fewer than five events per variable, then we will preselect a smaller group of the most relevant covariates or conduct a univariable analysis.

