#### Subgroup analyses

A subgroup analysis will be conducted on those mothers undergoing a trial of labour, excluding those who had a planned pre-labour cesarean delivery. Parity interaction terms will be omitted (and if they were significant in the main analysis, only nulliparous mothers will be analysed, as was done for the main analysis). Stepwise backward elimination will be conducted from the beginning, including either pre-pregnancy BMI or delivery BMI, whichever was chosen in the main analysis based on predictive value there.

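### Backward elimination in the primary cesarean model, rerun in the trial-of-labour subgroup, should give way to one covariate list fixed in advance; the effect is probably small, but so is the cost

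*Protocol article*

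**What the plan says.** For the primary outcome, the Analysis plan says: "For the primary outcome of cesarean delivery, backward stepwise Robust Poisson Regression will be used". The candidate list is introduced with "The following variables will be included in the multivariable Poisson regression model as potential predictors of cesarean section". Two entries, maternal BMI and gestational BMI gain, are marked as protected from removal. Everything else can be removed: parity, age, gestational age, height, race, smoking, payment type, onset of care, education, fertility treatment, diabetes, hypertension and the two parity interactions.

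No removal threshold is printed. The only pointer to the criterion is in the multiple-imputation paragraph: "P-values for the likelihood ratio test for each variable in each imputed dataset will be pooled using the median p-value rule".

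The same section takes the opposite line for the other endpoints: "For secondary outcomes, all explanatory variables will be retained in the model", and "Stepwise backward regression will not be used". Each secondary model has its own list. For rare outcomes, "If there are fewer than five events per variable, then we will preselect a smaller group of the most relevant covariates" or the analysis becomes univariable.

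For the trial-of-labour subgroup, the Subgroup analyses section says: "Stepwise backward elimination will be conducted from the beginning". The Sensitivity analysis section replicates the primary analysis with weight gain but does not say whether selection is rerun. Its complete-case check carries the final fitted model over unchanged. If there is a parity interaction, parous women are analysed separately, and no selection method is given for them.

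**The concern.** The objective in the Background section is to describe how BMI gain relates to cesarean delivery and to compare two BMI measures as predictors. Both exposures are forced into the model, so the remaining variables serve as adjustment. Selection on their own association with cesarean has three drawbacks for that purpose.

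- It ignores how strongly a covariate is tied to BMI or gain. A weak predictor of cesarean that is correlated with the exposure can be dropped although it confounds.
- The plan describes no allowance for selection. The final intervals would be read as if the covariate set had been fixed beforehand.
- Elimination is run separately in the main and trial-of-labour analyses, so the adjustment sets can differ. A change in the BMI or gain relative risk between them could then reflect the population or the covariates.

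The usual reason for elimination, too few events for the number of terms, does not apply here.

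**Working it through.** **1. Is there anything for parsimony to prevent?** The Sample size section gives 716,392 births at a cesarean rate of 27.40% (nulliparous) and 570,014 at 18.17% (full sample). Those sizes cannot be reproduced, because the R² values and the BMI-group prevalences are not printed; this point does not depend on them. The number of coefficients is an assumption.

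| Sample | Events | Per coefficient, 47 assumed | Per coefficient, 100 assumed |
|---|---|---|---|
| Nulliparous | 716,392 × 0.274 = 196,291 | 4,176 | 1,963 |
| Full | 570,014 × 0.1817 = 103,572 | 2,204 | 1,036 |

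The plan's own trigger for using fewer covariates in the rare-outcome models is five events per variable.

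**2. Planned precision.** With 90% power and a two-sided alpha of 0.05 (the sides are not stated), the target log relative risk is 1.96 + 1.28 = 3.24 standard errors (SE).

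- Nulliparous: ln(28.40/27.40) = 0.0358, so SE = 0.0358/3.24 = 0.0111.
- Full sample: ln(19.17/18.17) = 0.0536, so SE = 0.0536/3.24 = 0.0165.

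**3. Which covariates could be dropped?** Assume removal at p > 0.05 and a binary covariate with prevalence q. For robust Poisson regression, SE(log RR) is about √[(1 − π)/(π N q(1 − q))], where π is the cesarean rate. With N = 716,392 and π = 0.274:

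| q (assumed) | SE | Dropped if estimated RR is below | Kept 99% of the time if true RR is at least |
|---|---|---|---|
| 10% | 0.0064 | exp(1.96 × 0.0064) = 1.013 | exp(4.286 × 0.0064) = 1.028 |
| 3% | 0.0113 | 1.022 | 1.050 |

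Here 4.286 = 1.96 + 2.326. If the dropped covariate's prevalence differs by 0.1 to 0.2 across the exposure contrast (assumed), the exposure log RR shifts by 0.1 × 0.0126 = 0.0013 up to 0.2 × 0.0221 = 0.0044. That is 3.5% to 12% of the target of 0.0358.

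**4. What happens to the intervals?** Backward elimination was simulated in the large-sample normal limit. The assumptions were removal at |z| < 1.96, covariates independent of each other, true z of 1 to 2, and correlation of 0.1 to 0.3 with the exposure.

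| Setting | Coverage of nominal 95% interval |
|---|---|
| One weak covariate | about 93% to 95% |
| Three, all confounding in the same direction | about 82% to 94% |
| True z of 4 | near nominal (about 94% at worst) |
| True z of 6 | nominal |

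Bias in the two weak-covariate settings ran from about 0.05 SE to about 0.63 SE. The top of that range is 0.63 × 0.0111 = 0.007 on the log scale, a relative risk of 1.007, or 0.63/3.24 = 19% of the target. If one of three covariates acts in the opposite direction, bias falls to about 0.2 SE, although coverage recovers only in part. With an AIC-like removal rule, three same-direction covariates at correlation 0.3 give a bias of 0.22 to 0.31 SE and coverage of around 90%.

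**5. Effect of the likelihood-ratio criterion.** If the p-values come from the Poisson working likelihood, they overstate the variance of a binary outcome by about 1/(1 − π). A nominal 0.05 rule then acts like |z| < 1.96/√(1 − 0.274) = 2.30, so somewhat more covariates would be dropped than in steps 3 and 4.

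**The case against.** The method is disclosed, both exposures are protected, and the plausible effect is small. No removal rule is printed: p-value selection is inferred from the imputation paragraph, and a threshold may properly sit in a separate analysis plan. No covariate's z or correlation with BMI appears in the document, so the low coverage figures rest on assumed values. The Protocol validation section reports height and age as linearly associated with cesarean in the 2022 data, which makes their removal unlikely. All of this stands, and it limits the size of the point without answering it. The choice of elimination is stated, and no reason is given for it.

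Four stronger readings are tempting, and the document does not support them.

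- **Every deletion adds bias.** The list includes diabetes with a gestational category, hypertension in pregnancy and gestational age. The Secondary outcomes section lists diabetes, hypertensive disorders and preterm delivery as outcomes, so these covariates may lie downstream of BMI or gain. Removing a mediator need not bias a total effect.
- **The secondary models provide one common full list.** Each has its own. The perineal laceration model, for example, leaves out smoking, payment type and education, and rare outcomes may use fewer covariates still.
- **Adjustment sets will differ everywhere.** Rerun selection is explicit only for the trial of labour. For weight gain and for parous women it is merely possible.
- **The choice between pre-pregnancy and delivery BMI depends on elimination.** As written, the two models compared by AIC use the same covariates.

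**Conclusion.** The point holds as a weakness of method and comparability in the primary and trial-of-labour models. Elimination serves no purpose at this size, makes the reported intervals conditional on a data-chosen model, and can give the two analyses different adjustment sets.

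Its probable numerical effect is small. The exposure relative risk would shift by well under 1%: 0.1% to 0.4% in the dropped-covariate calculation, and about 0.7% at the top of the simulated range. Coverage stays at about 93% to 95% with one borderline covariate. A marked loss needs several borderline covariates correlated with the exposure and is worst when they act in the same direction. These figures assume p = 0.05 removal and the stated correlations and prevalences. The change is worth making because it is nearly free, not because the study's main conclusion is at risk.

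**What to change.** Delete backward elimination from the Analysis plan (primary outcome) and from Subgroup analyses. State one covariate list in advance and fit the primary, parous, trial-of-labour and weight-gain models with it.

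Let parity and its interactions follow the rule that sets the population. If interaction is found, the analyses restricted by parity carry no parity terms. If it is not, parity stays as a covariate and the interaction terms come out.

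Before fixing the list, decide on causal grounds, as was done for birthweight, whether diabetes, hypertension and gestational age belong in a model for the intended effect, and give the reason.

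The cost is a change of wording and fewer model fits. No further births are needed, because the sample size already took R² from regressions on the other explanatory variables. Intervals may be slightly wider if weak covariates correlated with the exposure are retained. In the extreme simulated case of three independent covariates at correlation 0.3, the full-model SE is 1/√(1 − 3 × 0.09) = 1.17 times the SE with all three removed; at correlation 0.1 the factor is 1/√(1 − 3 × 0.01) = 1.015. That extra width is uncertainty which the selected model would leave out.

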### Secondary outcomes

Secondary outcomes were clinically relevant outcomes available in the dataset.

Maternal
-Third- or fourth-degree perineal laceration-Instrumental vaginal delivery-Diabetes in pregnancy (pre-existing type 1 or type 2 diabetes or gestational diabetes)-Pre-term delivery-Hypertensive disorders in pregnancy-Induction of labour-Augmentation of labour-Chorioamnionitis in labour-Unplanned hysterectomy-Blood transfusion-Admission to intensive care unit (ICU)-Trial of labour

Neonatal
-Birth weight >90th percentile-Birth weight <10th percentile-Apgar Score < 6 at 5 min-Assisted Ventilation immediately following delivery-Assisted ventilation required for more than 6 h-Neonatal intensive care unit (NICU) admission-Antibiotics received for suspected neonatal sepsis-Seizure or serious neurological dysfunction-Infant breastfed at discharge

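### Mediators are handled inconsistently: birthweight is left out to keep the fetal-weight pathway, but gestational diabetes and hypertension in pregnancy are adjusted for, so the BMI relative risks are not total effects and may not carry the whole fetal-weight path

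*Protocol article*

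**What the plan says.** All the modelling statements are in the Analysis plan of the protocol article.

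- **Birthweight.** It is omitted on mediator grounds: "Birthweight will not be included as an explanatory variable because it was considered that fetal weight may be on the causal pathway". The stated consequence is that the RRs for BMI and BMI gain "will include any indirect effect mediated through fetal weight".
- **Diabetes and hypertension.** The candidate list for the same model contains "Diabetes (3 categories: pre-pregnancy, gestational, none") and "Hypertension in pregnancy (dichotomous"). No causal reason is given for either.
- **Selection.** "For the primary outcome of cesarean delivery, backward stepwise Robust Poisson Regression will be used". Only maternal BMI and BMI gain are protected from elimination.
- **Exposure.** AIC decides which BMI variable is "to be used in subsequent analyses (either pre-pregnancy or delivery BMI").
- **The same conditions as outcomes.** The Secondary outcomes section lists "Diabetes in pregnancy (pre-existing type 1 or type 2 diabetes or gestational diabetes") and "Hypertensive disorders in pregnancy".
- **Other analyses.** The Sensitivity analysis section has two items: weight gain in place of BMI gain, and a complete-data comparison if imputation is used. Neither removes diabetes or hypertension, and nor does the trial-of-labour subgroup analysis as described.

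**The concern.** The plan applies a causal rule to one variable: do not adjust for something that may lie between BMI and cesarean delivery. Gestational diabetes and pregnancy-onset hypertension can also arise after the exposure, and the plan studies both conditions as outcomes. It nevertheless conditions on them without explanation.

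Two things follow. First, the BMI-category RRs keep one group of indirect paths (through fetal weight) and remove others (through diabetes and hypertension), and a reader is not told so. Second, the plan's own statement about fetal weight may fail. If gestational diabetes alters fetal weight, adjusting for it closes the path from BMI through gestational diabetes and fetal weight to cesarean delivery.

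This affects what the main result can be said to show. The Uniqueness section says the study will look at how BMI acts on outcomes and by which mechanisms, so readers will probably take the RRs as the effect of BMI.

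**Working it through.** **The plan's own figures.** The protocol states no figure for mediation or attenuation, so there is none to reproduce. The sample-size figures do not bear on this point, except to show how large the data set is.

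**Step 1. Could stepwise selection remove the two covariates?** This is unlikely. Take the smaller required sample (570,014), the stated cesarean rate (18.17%), and, as assumptions, a condition with 4% prevalence and a cesarean RR of 1.2.
- Expected cesareans among those with the condition: at least 570,014 × 0.1817 × 0.04 ≈ 4,143.
- Approximate standard error of the log RR: 1/√4,143 ≈ 0.0155.
- z ≈ ln(1.2)/0.0155 = 0.182/0.0155 ≈ 12.

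This ignores correlation with other covariates, but the margin is wide.

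**Step 2. Size for a BMI category read as a total effect.** Assume a log-linear model with two binary mediators that are independent given BMI. For each mediator, the factor that adjustment removes is

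F = [1 + g1(r − 1)] / [1 + g0(r − 1)],

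where g1 and g0 are the mediator's prevalence in the higher-BMI and normal-BMI groups and r is its cesarean RR. The two factors multiply. **All inputs below are assumptions; the protocol gives none.** They compare Class 3 obesity with normal BMI, with g0 = 4% for gestational diabetes and 6% for hypertension.

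| Case | Gestational diabetes (g1, r) | Hypertension (g1, r) | Product | Total RR 2.00 would read |
|---|---|---|---|---|
| Low | 12%, 1.2: 1.024/1.008 = 1.016 | 18%, 1.3: 1.054/1.018 = 1.035 | 1.05 | 1.90 |
| Midpoint | 16%, 1.3: 1.048/1.012 = 1.036 | 23%, 1.5: 1.115/1.030 = 1.083 | 1.12 | 1.78 |
| High | 20%, 1.4: 1.080/1.016 = 1.063 | 28%, 1.7: 1.196/1.042 = 1.148 | 1.22 | 1.64 |

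**Step 3. A second assumed set, for obesity in general.** Gestational diabetes 5% v 8–15% with RR 1.1–1.4; hypertension 8% v 12–20% with RR 1.2–1.6.
- With a direct RR of 1.20, the total RR is 1.21 to 1.33, so adjustment removes about 6% to 37% of the log RR.
- With a direct RR of 1.50, the total RR is 1.52 to 1.67, so adjustment removes about 3% to 21%.

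**Step 4. Does the direction always hold?**
- *BMI categories.* In each assumed scenario where higher BMI raises both conditions and both raise cesarean delivery, the adjusted RR was nearer 1. An underweight example behaved the same way (total 0.887, adjusted 0.900). In a simulation with an unmeasured common cause of mediator and outcome, adjustment moved the RR from 1.200 to 1.185.
- *BMI gain.* The direction can reverse. If a diabetes diagnosis lowers later gain and diabetes raises cesarean risk, diabetes confounds the gain estimate, and leaving it out pulls that estimate down. A simulation on assumed inputs gave 1.0155 per unit unadjusted and 1.0191 adjusted. It shows direction only.
- *Delivery BMI.* If AIC selects it, gestational diabetes can precede the exposure, so it may act partly as confounder and partly as mediator.

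**The case against.** The strongest reply is that the protocol never claims a total effect. Its objective, in the Background, is to describe a relationship and compare predictors, and the covariates are introduced as potential predictors. An RR that includes the fetal-weight path and is conditional on diabetes and hypertension is close to what the text promises. This stands, with two limits: a purely predictive model has no causal reason to omit birthweight, and the promise covers *any* effect through fetal weight, which fails if gestational diabetes affects fetal weight.

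A reader might infer four stronger points. The documents do not support them.
- **That the RRs are certainly biased toward the null.** This needs a total-effect target, which is not declared, and mediated paths that run the same way as the direct effect. It does not carry over to BMI gain.
- **That diabetes and hypertension are on the pathway just as birthweight is.** The diabetes covariate and outcome both include pre-existing disease, plausibly a confounder, and hypertension is not defined as new-onset. Listing a condition as a secondary outcome does not by itself declare it a consequence of BMI.
- **That dropping the two covariates gives a total-effect model.** Gestational age stays in although preterm delivery is a secondary outcome. BMI gain also stays in and, with pre-pregnancy BMI as exposure, is itself downstream.
- **That the attenuation threatens power.** The design RRs (19.17/18.17 = 1.055 overall, 28.40/27.40 = 1.036 in nulliparous women) are detection targets. Reading 1.78 instead of 2.00 endangers neither detection nor the hypothesis of rising risk.

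**Conclusion.** The inconsistency is real and lies within one section: one possible mediator is excluded for a stated reason, and two probable ones are adjusted for with none given. The BMI-category RRs are conditional on diabetes and hypertension. They are not total effects, and if gestational diabetes affects fetal weight they do not contain all of the fetal-weight path.

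Read as total effects, they are likely attenuated. The size is unknown from the protocol. The 1.05 to 1.22 range for Class 3 obesity rests wholly on assumed prevalences and RRs, and on independent mediators in a log-linear model. For BMI gain, or with delivery BMI as exposure, no direction can be claimed. The point concerns interpretation and one missing parallel analysis. It does not show that the planned model is invalid or must be replaced.

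**What to change.** 1. Prespecify, alongside the planned primary model, a BMI model without gestational diabetes and pregnancy-onset hypertension. Keep pre-pregnancy diabetes, and chronic hypertension if the file separates it. Report both models.
2. Label the planned BMI RRs as conditional on diabetes and hypertension.
3. Correct the fetal-weight sentence: the planned RRs include effects through fetal weight only in so far as these do not run through the adjusted conditions.
4. Do not call the added model a total-effect model while gestational age and BMI gain remain in it.
5. Keep the adjusted model for the BMI gain estimate, because without the diabetes term that estimate may be confounded by diabetes diagnosis.

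The cost is one extra model on public data, a few sentences of text, and two sets of BMI RRs to explain.

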#### Exclusion criteria

Exclusion criteria will include:-Stillbirths (as the stillbirth dataset does not include maternal weight at delivery)-Multiple pregnancies-Non-cephalic presentations-Previous cesarean delivery-Maternal age < 16 years or maternal age > 49 years

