### Variables

Mean and standard deviation (SD) will be used to describe continuous variables if they are normally distributed, otherwise median, and interquartile range (IQR) will be used. Categorical variables will be reported as numbers and percentages.

Gestational BMI gain in kgm^-2^ will be reported in the primary analysis. GWG in kg will be analysed for the sensitivity analysis.

Variables will be measured/described as follows:-Gestational BMI gain in kgm^-2^ (for the main analysis). Analysed as a linear spline with a knot at 5 kgm^-2^ based on preliminary analysis of 2022 data.-Self-reported pre-pregnancy BMI in kgm^-2^ (based on height and self-reported pre-pregnancy weight) classified according to the Institute of Medicine (IOM) groups [15]-Measured BMI at birth in kgm^-2^ classified into groups of the same size as pre-pregnancy BMI to account for expected weight gain during pregnancy-GWG in kg (for the sensitivity analysis)-Parity (categorized as nulliparous, or parous)-Maternal age in years (as a continuous variable, with linearity observed in the preliminary analysis of the 2022 data)-Gestational age at birth in weeks (categorized by gestational week)-Maternal height in cm (as a continuous variable, with linearity observed in the preliminary analysis of the 2022 data)-Maternal race (to be categorized as the dataset allows)-Maternal cigarette smoking during pregnancy (to be categorized as the dataset allows)-Payment type (public/private)-Trimester of onset of maternity care (first/second/third trimester/no antenatal care)-Maternal education (categorized as (i) 8th grade or less, (ii) 9th-12th grade, no diploma, (iii) completed high school or GED, some college credit or associate degree, (iv) bachelor’s degree, (v) masters degree, doctorate or professional degree)-Any fertility treatment used in conception (yes, no, unknown)-Diabetes in pregnancy (to be categorized as the dataset allows)-Hypertensive disorders in pregnancy (to be categorized as the dataset allows)-Previous preterm birth (yes, no)

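### The trial-of-labour model names gestational diabetes only, so one secondary outcome may carry residual, probably small, confounding by pre-existing diabetes

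*Protocol article*

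**What the plan says.** The article describes diabetes in four places.

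- Secondary outcomes: diabetes is itself an outcome and covers both types, "Diabetes in pregnancy (pre-existing type 1 or type 2 diabetes or gestational diabetes".
- Variables: there is one study variable, "Diabetes in pregnancy (to be categorized as the dataset allows".
- Analysis plan, primary model: the candidate covariates include "Diabetes (3 categories: pre-pregnancy, gestational, none".
- Analysis plan, trial of labour: the list has delivery BMI, BMI gain, parity, age, gestational age, height, race, payment type and education, and closes with "trimester of onset of maternity care, use of ARTs, and gestational diabetes".

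The exclusion criteria remove stillbirths and "Multiple pregnancies-Non-cephalic presentations-Previous cesarean delivery-Maternal age < 16 years or maternal age > 49 years". Pre-existing diabetes is not among them, so these women are in the analysis set. The article does not say how they are coded in the trial-of-labour model, nor why the term is narrower there. Where it does explain an omission, that of birthweight, the reason is that "fetal weight may be on the causal pathway between BMI or BMI gain and cesarean delivery".

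**The concern.** A yes/no term for gestational diabetes has two groups. Women with type 1 or type 2 diabetes before pregnancy do not have gestational diabetes, so on a literal reading they join women without diabetes in the reference group. If pre-existing diabetes is more common at higher BMI and makes a planned pre-labour cesarean more likely, the BMI relative risks for trial of labour take up part of its effect, mostly in the highest BMI groups.

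The narrower term also fits neither of the two usual aims. If the aim is to control confounding, the diabetes that predates the pregnancy is the first type to include. If the aim is a total effect of BMI, the diabetes that arises during pregnancy is the first type to leave out. The list does the reverse in both cases.

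At stake are the estimates for one of 21 listed secondary outcomes. In a cohort of this size (the required samples for cesarean delivery are 570,014 and 716,392), a shift of a few percent would not be hidden by random error.

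**Working it through.** **Step 1. The two lists side by side.**

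| | Primary model | Trial-of-labour model |
|---|---|---|
| Pre-existing diabetes | own category | not named |
| Gestational diabetes | own category | named |
| No diabetes | own category | reference, by implication |
| Smoking | listed | not listed |
| Hypertension | listed | not listed |

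The mismatch is real and unexplained. Diabetes is not the only difference: smoking and hypertension are missing as well.

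**Step 2. How large could the effect be?** The article gives no sample size, effect or prevalence for this model, so there is no stated figure to reproduce. For scale I used the bias factor for one omitted binary covariate:

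factor = [1 + p1(RR − 1)] / [1 + p0(RR − 1)]

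Here p1 and p0 are the prevalence of pre-existing diabetes in the highest and the reference BMI group, and RR is its relative risk for the modelled event. All three are assumptions. The formula takes RR as constant across BMI groups and ignores the other covariates.

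| p0 | p1 | Having a trial, RR 0.95 | Having a trial, RR 0.70 | No trial, RR 1.5 | No trial, RR 3 |
|---|---|---|---|---|---|
| 0.3% | 2% | 0.9991 | 0.9949 | 1.0085 | 1.0338 |
| 0.5% | 4% | 0.9982 | 0.9895 | 1.0175 | 1.0693 |
| 1% | 6% | 0.9975 | 0.9850 | 1.0249 | 1.0980 |
| 0.5% | 8% | 0.9962 | 0.9775 | 1.0374 | 1.1485 |

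The extremes written out:

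- Having a trial, smallest shift: (1 − 0.02 × 0.05) / (1 − 0.003 × 0.05) = 0.99900 / 0.99985 = 0.999.
- Having a trial, largest shift: (1 − 0.08 × 0.30) / (1 − 0.005 × 0.30) = 0.9760 / 0.9985 = 0.978.
- No trial, smallest shift: (1 + 0.02 × 0.5) / (1 + 0.003 × 0.5) = 1.0100 / 1.0015 = 1.008.
- No trial, largest shift: (1 + 0.08 × 2) / (1 + 0.005 × 2) = 1.16 / 1.01 = 1.149.

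**Step 3. Why the two scales differ.** Suppose 10% of women without pre-existing diabetes have no trial of labour (assumed) and pre-existing diabetes doubles that to 20%. The relative risk for having a trial is then 0.80 / 0.90 = 0.889. With prevalences of 5% and 0.5%:

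- No trial: 1.05 / 1.005 = 1.045.
- Having a trial: (1 − 0.05 × 0.111) / (1 − 0.005 × 0.111) = 0.995.

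The same confounding shifts the estimate by 4.5% on one scale and 0.5% on the other. The article names the outcome as trial of labour, so the smaller scale applies to the model as written.

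These figures are for BMI group. I did not size the effect on the BMI-gain relative risk, because the article gives nothing on how pre-existing diabetes relates to BMI gain.

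**The case against.** **The coding is not stated.** The phrase may be shorthand for the single diabetes variable in the Variables section. The same sentence also uses a looser label for fertility treatment than the primary list does. This stands: a reader might infer that women with pre-existing diabetes are definitely counted as non-diabetic, but that is only the literal reading. If the wording is merely loose, the same edit settles it.

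**Pre-existing diabetes may not be a pure confounder.** Longstanding high BMI can precede type 2 diabetes, so part of its effect may lie on the BMI pathway, and leaving it out would then move the estimate towards a total effect. This stands in part, and it is why I say the estimates may be confounded, not that they are. It does not justify the list as written. The list keeps gestational diabetes, which arises in pregnancy, and the primary model adjusts for both types. Pre-existing diabetes also comes before gestational BMI gain, so it cannot mediate that exposure.

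**The bias formula is crude.** Age, race, payment type, education and the other listed covariates may absorb part of the effect. This stands, so the computed range could overstate the residual distortion.

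**Shorter lists are a design choice.** The rule "For secondary outcomes, all explanatory variables will be retained in the model" might be read as contradicting the trial-of-labour list. It does not: the next sentence concerns stepwise elimination, outcome-specific lists follow, and the perineal-laceration list has no diabetes term at all. The point rests on the mismatch in the diabetes variable, not on that rule.

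**Conclusion.** The point holds in a limited form. The trial-of-labour list names one type of diabetes where the primary model separates two, the women concerned are not excluded, and no reason is given. Taken literally, the BMI and BMI-gain relative risks for this outcome may carry residual confounding by pre-existing diabetes.

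The size is probably small. On assumed inputs, the factor for the highest against the reference BMI group is about 0.98 to 1.00 for having a trial of labour. If the event is turned round to not having one, it is about 1.01 to 1.15. The direction assumes that pre-existing diabetes is more common at high BMI and lowers the chance of a trial of labour; the article gives figures for neither.

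A reader might go further and infer that the explanation of the primary cesarean result is biased. The documents do not support that. The primary model has the three-category variable, and nothing says that the trial-of-labour model will be used to interpret the primary result. The subgroup analysis of women undergoing a trial of labour runs its own backward elimination and is not tied to this list.

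**What to change.** In the Analysis plan's trial-of-labour covariate list, replace gestational diabetes with the three-category diabetes variable already defined for the primary model. If the narrower term is intended, state why, and say how women with pre-existing diabetes are coded.

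The cost is one changed covariate that is already to be derived for the primary model: no new data, and no effect on the primary analysis or its sample size. The swap does not fully align the two lists, since smoking and hypertension would still be absent; one sentence giving the reason for those omissions could be added in the same edit.
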